##### Qualitative data collection

Readiness interviews will consist of open-ended questions that will be asked of IC stakeholders at the system, provider, and client levels. These include 20 administrators, 20 school nurses, and 20 individuals randomly selected from the IRTs (*n* = 60). Interviews will explore if the necessary conditions exist for implementation and sustained use of the EB strategies and how best to optimize them. Questions will center on attitudes toward, access to, and availability of school and community supports for (a) suicide prevention, (b) LGBTQ youth, and (c) school nursing staff. Verbal and written information regarding school policies and practices pertinent to EB strategies will be collected. Specific questions will focus on transgender and intersex youth, i.e., perceptions and knowledge related to their risks for suicide, substance use, bullying, and truancy within school settings, and extant support. Finally, interviews will address pragmatic concerns (e.g., staffing and resources) and organizational factors (e.g., leadership and supportive culture/climate) [43, 47, 48, 62]. Results of these first assessments will inform IRT efforts to build implementation capacity and subsequent plans to implement and sustain EB strategies. For comparison purposes, a complementary set of interviews will be completed with the 20 nurses and the 20 administrators in the CC schools.

##### Qualitative data analysis

All qualitative interviews will be digitally recorded and professionally transcribed. Hand written notes will be organized according to a standard format, with information on date, time, and length of the interaction, setting, and participants involved. Typed notes and transcripts will be imported into a password protected NVivo database for efficient organization and analysis via iterative readings or codings [63]. Responses will first be analyzed by “open coding” to discover themes, ideas, and issues; a coded index of topics addressed in the data will next be developed. “Focused coding” will then be used to determine which topics arise often and which represent unusual or particular concerns [64, 65]. NVivo search functions can quickly locate and cross-reference statements of interest from participants (e.g., all text coded with “bullying at school,” “nonjudgmental teachers,” and “implementation barriers”) to examine relationships in the data within and across participant groups (e.g., school nurse, administrator, and IRT member).

Interview findings will be triangulated across participant types, creating a matrix (a) describing specific themes related to key study issues outlined in the EPIS model, and (b) supporting data by participant type. A side-by-side comparison of the various perspectives will be used to identify points of convergence and divergence in all participant statements related to the themes under consideration. In this staged approach to analysis, sets of notes and transcripts will be coded and detailed memos that describe and link codes to each theme and issue will be created. Discrepancies in coding and analysis will be identified during this process and resolved during regular team meetings.

##### Quantitative data collection

The 40 administrators and 40 school nurses in both the IC and CC schools will complete the first of an annual 30-min web-based survey that assesses organizational characteristics of schools and administrator/nurse work attitudes.

*Measures*. Demographics include age, gender, sexual orientation, race/ethnicity, education, employment, experience, geographical area of work, and activities performed in schools. Attitudes toward sexual and gender minorities will be assessed through two validated and reliable instruments, the *Attitudes Toward Lesbians and Gays Scale *[66] and the *Attitudes Toward Transgender Individuals Scale *[67]. Organizational culture and climate will be assessed via the *Organizational Social Context Scale*, which has good psychometric properties with Cronbach’s alphas ranging from 0.78 to 0.94 [42]. Climate includes three domains that affect use of EB strategies: (1) stress; (2) engagement; and (3) functionality. Culture includes (1) proficiency (responsiveness, competence) and (2) resistance (apathy, suppression). Work attitudes consist of two measures, *job satisfaction* (ten items) and *organizational commitment* (13 items), with good reliability and validity [68–70]. Attitudes toward adopting EB strategies will be assessed using the *Evidence-Based Practice Attitude Scale*, which examines: (1) intuitive appeal of EB practices; (2) likelihood of adopting if required; (3) openness; and (4) perceived divergence between EB practices and current practice [71]. Leadership will be measured via the *Multifactor Leadership Questionnaire (MLQ) *[72]. The MLQ assesses transformational leadership, transactional leadership, passive/avoidant leadership (laissez-faire), and perceived outcomes of leadership (extra effort, effectiveness, satisfaction). The MLQ has good psychometric properties with Cronbach’s alphas ranging from 0.76 to 0.90 [41, 69]. School-community linkages will be measured through an LGBTQ-specific modification of the *Collaborating with Community Subscale*, an eight-item tool based on the Measure of School, Family, and Community Partnerships [73]. This tool rates school partnership practices for integrating resources and services from the community to strengthen school programs, learning, and well-being for LGBTQ students on a scale of 1 (not occurring) to 5 (extensively occurring) and offers insight into improvement areas and future directions. An adapted *Assessment of *
*Climate Embedding Mechanisms*
*(ACEM)* measure will elicit Likert scale ratings on how frequently each EB strategy is used, EB strategy adherence, and school leadership support [43]. In year 1, it will be completed by nurses and administrators to serve as a baseline assessment for each school.

*School administrative data*. Publicly-available administrative data will be used to assess faculty and staff retention, school truancy, graduation rates, drop-out rates, extracurricular student activities, and overall student characteristics, e.g., socioeconomic status and race/ethnicity, at participating schools.

##### Quantitative data analysis

Quantitative analysis of the web-based surveys will involve descriptive analyses, aggregated at the school level, for each subscale in the organizational web-based survey. Data will be compared across schools to determine areas of relative strength and weakness regarding factors known to impact implementation. Data will be shared with the IC IRTs in the form of feedback reports comparing each school’s scores on each subscale to the average scores across other schools. The raw data, feedback, and recommended changes will help ensure that the IRTs recognize barriers that could affect implementation and will provide impetus for the IRTs to enhance deficit areas. For example, if the data reveal that a school has a defensive climate, an IRT can then determine ways to work under this constraint or, alternatively, to improve the climate. The analysis of school administrative data will also involve descriptive analyses of staffing, faculty/staff retention, truancy, graduation and drop-out rates, extracurricular student activities, and overall student characteristics, which will be compared across schools to identify potential confounders.

##### Feedback reports

After completing qualitative and quantitative analyses, the research team will prepare summaries that describe issues, ideas, and concerns raised by the school nurses, administrators, and IRTs at the IC schools, implementation readiness at the school and staff levels, and the encompassing school context. These summaries will include contextual detail for nuanced implementation planning through the DAP and outline strengths and weaknesses in the school settings that may influence implementation and uptake of each of the EB strategies. No feedback will be provided to the CC schools until the final year of the project.

#### Preparation phase

The IRTs review data from the exploration phase in the preparation phase to determine (a) adaptations needed in the school context and its workforce to ensure uptake; and (b) how to accomplish such adaptations. The school-specific feedback reports made available to the IRTs will provide information on relative strengths and weaknesses and key areas for the IRTs to address when implementing the strategies. Each school nurse-led IRT will review their relevant report, analyzing the extent to which their schools possess the requisite conditions for implementing each strategy. The nurse champion will guide the IRT through a process for prioritizing and addressing recommendations [74], weighing each based on five dimensions (importance, cost, time, commitment, and feasibility). The IRT would then outline the steps needed to follow through with actions. If a potential action is deemed “infeasible” at that time, the nurse would encourage the IRT to consider more “workable,” short-term strategies to create conditions sufficient for implementation.

Coaching for IC schools begins in the preparation phase. Coaches will engage in monthly conference calls with each nurse-led IRT supplemented with bi-monthly visits to the IC schools to identify additional training needs and create Resource Guides and Referral Lists to support practices related to the EB strategies. The guides will contain written material about advancing EB strategies, and the lists will identify community health and mental health providers and resources for LGBTQ youth and their peers. Coaching staff have specialized expertise in team building, school climates, LGBTQ youth intervention, suicide prevention, and transgender populations. Their role is to improve school nurse and IRT performance through both training and technical assistance (including development and delivery of webinar content), enabling them to hone the knowledge and skills for meeting EB strategy implementation goals.

#### Implementation phase

Training with adaptation support begins in the implementation phase. Twenty nurse-led IRTs will annually implement or strengthen a minimum of two of the six EB strategies per year, building on lessons accumulated over time. Ongoing assessment will occur to optimize local adaptations to enhance implementation. Fidelity and adherence data will be collected and provided as feedback to coaches and IRTs.

The overall training will emphasize explicit inclusion and discussion of adaptation, i.e., why and what to adapt, when to seek guidance on adaptation, and how to use the coaches and IRT. Further augmentation may be accomplished by including materials and training in response to unique school level barriers or populations (e.g., lack of LGBTQ-inclusive anti-bullying policies or negative teacher attitudes about LGBTQ youth). School nurses will be provided with a one-day in-person training that coincides with an annual conference sponsored by the NM School Nurses Association. The training will cover leadership that supports effective EB strategy implementation. To prepare nurses to be strong change agents in schools and to negotiate interdisciplinary IRTs, adapted modules (e.g. development of positive IRT climates and organizational support for EB strategies) of an implementation leadership curriculum that features traditional didactics and role-play activities are included in the training. The modules will be reinforced through regularly scheduled coaching and annual in-person booster trainings for school nurses in the implementation phase [75]. The IRTs will also benefit from eight 1-h webinars on LGBTQ people, youth suicide prevention, and school safety and supports. Trainees will receive monetary incentives or continuing medical education (CME) credits.

Coaching in deployment of the strategies will occur during the implementation phase. Coaches will continue to organize monthly conference calls with each IRT and conduct bi-monthly visits to IC schools to provide technical assistance. These efforts are intended to enhance the likelihood that EB strategies are implemented in the IC schools, and will contribute to adjustments to school-specific implementation protocols, if warranted. Coaches will compile logs of interactions with nurses and IRTs, which will be analyzed for process evaluation.

#### Sustainment phase

During the sustainment phase, the IRT analyzes implementation successes and challenges, focusing on school nurse and member satisfaction, adherence and fidelity to action plans, use of EB strategies, and the NM YRRS outcomes over time.

### Aim 2: conduct a cluster randomized controlled trial to assess whether LGB youth and peers in RLAS intervention schools report reduced suicidality, depression, substance use, and bullying, and increased safety compared to control schools

A cluster randomized controlled trial will assess whether LGBTQ students and their peers in RLAS intervention schools report reductions in suicidality, depression, substance use, bullying, and truancy related to safety concerns compared to those in usual care schools. Additional file 2 provides a study-specific checklist of information to include when reporting a cluster randomized trial. Additional file 3 contains a flow diagram of the phases of the randomized trial for the IC and CC schools. Randomization will take place in the exploration phase, as noted previously. Mahalanobis distance metric matching will be used to create pairs of similar schools [76], where one school in each pair will be randomly assigned to the IC.

The 2015 NM YRRS will offer baseline data for all schools and the 2017 and 2019 NM YRRS will yield follow-up data for the implementation and sustainment phases. From each school an average of 150 students complete the NM YRRS, for a sample size of 6000 per survey administration. Demographic data include gender, age, race/ethnicity, and sexual identity. Primary outcome measures assess suicide-related outcomes (“During the past 12 months, did you ever seriously consider attempting suicide?” “During the past 12 months, did you make a plan about how you would attempt suicide?” “During the past 12 months, how many times did you actually attempt suicide?”). Secondary measures assess depression (“During the past 12 months, did you ever feel so sad or hopeless almost every day for two weeks or more in a row that you stopped doing some usual activities?”), substance use (“During the past 30 days, on how many days did you have at least one drink of alcohol?” “During the past 30 days, how many times did you use marijuana?”), bullying (“During the past 12 months, have you ever been bullied on school property?”), and school safety (“During the past 30 days, on how many days did you not go to school because you felt you would be unsafe at school or on your way to or from school?”).

Analysis will examine five hypotheses using NM YRRS data: (1) IC schools will have a greater reduction in suicide-related outcomes than CC schools; (2) IC schools will have a greater reduction in depression than CC schools; (3) IC schools will have a greater reduction in substance use outcomes than CC schools; (4) IC schools will have a greater reduction in bullying than CC schools; and (5) IC schools will have a greater improvement in school safety than CC schools. Each analysis assesses these effects for the entire population and whether they are more pronounced for LGB students. The five outcomes predicted in hypotheses 1–5 will likely be more pronounced for LGB students, relative to other students. As the NM YRRS does not include items addressing gender identity, interviews and focus groups with school nurses, administrators, and IRT members will elucidate perceived impacts on transgender and intersex youth.

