## Background

In 2012, the United States (U.S.) Surgeon General identified lesbian, gay, bisexual, transgender, and queer or questioning (LGBTQ) youth as at heightened risk for suicide [1]. Risk factors include depression, substance use, inadequate social support, and not feeling safe at school [1–7]. Large population-based studies over the past 15 years have found that lesbian, gay, and bisexual (LGB) youth are at two to four times increased risk for suicidal ideation and attempts when compared to their cisgender, heterosexual peers [1–3, 5, 8–16]. Within LGB populations, suicidality disproportionately affects racial and ethnic minorities, including American Indian and Hispanic people [1, 17, 18]. In numerous surveys and qualitative studies, transgender youth report elevated risk for suicide, depression, and substance use [19–24].

In general, LGBTQ youth report high levels of rejection, harassment, victimization, violence, and sexual abuse that can contribute to mental health problems and suicide behaviors [3, 9, 13, 18, 25]. These behaviors relate to “minority stress,” i.e., chronic stress from stigmatization, prejudice, and discrimination [26]. National school climate surveys have found that LGBTQ youth are often exposed to minority stress in schools [25, 27]. Youth describe being victimized because of their known, or perceived, sexual orientation or gender identity [8–11, 13, 19, 27]. LGBTQ youth are also more likely to experience high school victimization when they disclose their orientation, self-identify as a sexual minority, recognize same-sex feelings at a younger age, or demonstrate gender-atypical behavior [14, 28].

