## Methods/Design

### Study context

This work will occur in New Mexico (NM) high schools. Sociodemographic and minority stress factors contributing to adverse psychosocial outcomes are common in NM, which ranks 43rd in personal income per capita ($34,133) and second in persons below the poverty level (20.2 %) [51]. Of NM’s 33 counties, 32 are medically underserved [52]. Suicide rates for NM youth, ages 15 to 24, are nearly twice the national rate (19.7/100,000) [53, 54]. American Indian and Hispanic people comprise almost 56 % of 2,085,287 NM residents [55] and, like LGBTQ people, are disproportionately affected by health disparities [56, 57].

The New Mexico Youth Risk and Resiliency Survey (NM YRRS) is part of the nationwide CDC Youth Risk Behavior Surveillance System. The NM YRRS is administered to high school students in odd-numbered years and uses two discrete population-based sampling designs. A smaller sample provides data representative of the state and a larger sample furnishes data on specific populations not well represented in the smaller state sample. In 2013, data from 5451 students were obtained for the statewide sample and data from 19,080 students were obtained for the larger sample. A minority of students, 26.1 %, were White, non-Hispanic. Hispanics comprised 59.2 % of the population, African Americans, 0.9 %, and other races/ethnicities, 13.7 %. Half (48.8 %) of students were female [58]. Suicidality rates among NM students far exceeded national averages; 15.6 % seriously considered suicide, 13.7 % planned an attempt, and almost 1 in 10 (9.4 %) attempted it in the last year [59].

The 2013 NM YRRS was the first to include questions about same-sex sexual contact and sexual identity of NM high school students, which enables the NM Department of Health and schools to better understand the health and safety risks of students. Almost 11 % of the sample identified as LGB, with 3.0 % identifying as lesbian or gay and 7.5 % as bisexual [60]. In NM, LGB students experienced a relative lack of safety at schools: 35.5 % reported being bullied on school property in the last year, compared with 17.0 % of their straight peers; 17.3 % skipped school because of safety concerns, compared with 5.6 % of their peers [61]. Suicidality rates among NM LGB students were strikingly high with 38.3 % considering suicide, 35.4 % reporting making a suicide plan, and 28.5 % attempting suicide in the past year [61].

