### Study design

This 5-year cluster randomized trial will include 40 NM high schools that employ a nurse on staff (*n* = 64). The schools will be randomized into the RLAS intervention condition (IC; *n* = 20) or the control condition (CC; *n* = 20). Cluster randomization was chosen because the intervention will be delivered at the school level. Schools will be eligible if they express interest in the full intervention and the school nurse and a lead administrator agree to participate and support the project. To minimize confounding effects, eligible schools will share the following characteristics: (1) public high school; (2) school nurse willingness to convene an IRT if randomized to the IC group; and (3) informed written consent from the school nurse to participate for four years. Additional file 1 contains confirmation of ethical approval.

From the IC schools, there will be three study populations: (1) school nurses; (2) school administrators; and (3) IRT members. From CC schools, there will be two study populations: (1) school nurses and (2) school administrators. School nurses and IRTs in the IC schools will receive innovation supports to encourage greater implementation of the six EB strategies (see Table 1). Nurses in the IC will recruit IRT members (4–6 people) willing to work with them on implementing the six EB strategies. These nurse champions will function as coordinators who keep the IRTs motivated, cohesive, and focused on goals; gain administrative buy-in during the Preparation Phase; and facilitate IRT planning in the Implementation Phase.

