#### Data analysis

Students are nested within school by time period groups (e.g., 2015 observations of one school), and these repeated observations of a school are each nested within one school. Hence, all quantitative models examining hypotheses will use multilevel modeling (i.e., hierarchical linear modelling) to conservatively adjust estimates for variability arising in outcomes due to student (level 1) nesting within school by time groups (level 2) and these repeated observations at the school level being nested within schools (level 3). Thus, all models will be run as random intercept regressions. Sampling weight and design information will be used to appropriately weight cases in analyses via multilevel pseudo maximum likelihood methods [77, 78] and Mplus^©^ [79]. Models for continuous variables will be run assuming normally distributed, continuous outcomes (unless descriptive analyses indicate zero-inflated Poisson models for count outcomes). Binary outcomes will be treated as having a binomial distribution and use a logit link function. Regression models (one for each measured outcome in all hypotheses) will regress the outcome on a dummy contrast representing study condition; a dummy contrast representing LGB; two contrasts representing linear and quadratic, i.e., u-shaped, change; the orthogonal interactions between condition and change contrasts; the orthogonal interactions between LGB, condition, and change contrasts; and all other component interactions not mentioned. These models represent whether (a) there was differential change as a function of condition and (b) whether this differential change was more pronounced among LGB students.

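### LGB status is recorded after randomisation, so the LGB × condition × change term would absorb any difference between arms in who comes to identify as LGB

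*Protocol article*

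**What the plan says.** All in the Protocol article:

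- **Source of LGB status.** Aim 2 lists sexual identity among the survey's background items: "Demographic data include gender, age, race/ethnicity, and sexual identity". The outcome items come from the same survey.
- **Timing.** The 2015 survey is baseline, and "the 2017 and 2019 NM YRRS will yield follow-up data for the implementation and sustainment phases". Schools are randomised in the exploration phase, before the follow-up waves.
- **Data structure.** Data analysis (Aim 2) nests students in school-by-wave groups and those groups in schools. Schools are followed over time; no link between a student's answers at different waves is described.
- **Model.** Each outcome is regressed on condition, an LGB dummy, linear and quadratic change, and all their interactions. The three-way term is read as whether differential change was larger among LGB students.
- **Prediction.** Aim 2 expects that the five effects "will likely be more pronounced for LGB students, relative to other students".
- **Intervention.** Table 1 lists safe spaces, a ban on harassment, staff development and inclusive curricula, among other strategies. The Background reports that "LGBTQ youth are also more likely to experience high school victimization when they disclose their orientation" and lists self-identification as a further risk factor.

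**The concern.** Sexual identity is handled as a fixed demographic, like age. At follow-up it is a self-report made in a school that has been exposed, or not, to the intervention. If being openly LGB costs less in intervention schools, some students there may identify as LGB who would not have done so in a control school. The LGB groups in the two arms would then contain different kinds of students, and randomisation would not make them comparable.

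The three-way term cannot separate this change of composition from a change in students' risk. The trial could report a larger benefit among LGB students when no student was helped, or fail to show a real one. Since the trial's stated purpose is to reduce suicide among LGBTQ youth, this contrast is likely to be read closely.

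There is a second consequence. With the LGB dummy and all its interactions in the model, the condition × change term may itself be conditional on LGB status. Under 0/1 coding it is the effect in non-LGB students, not in all students. The article refers to dummy contrasts and to orthogonal interactions, which does not settle the coding.

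**Working it through.** **Sample size stated in the plan.** "This 5-year cluster randomized trial will include 40 NM high schools that employ a nurse on staff" and "From each school an average of 150 students complete the NM YRRS, for a sample size of 6000 per survey administration": 40 × 150 = 6000 per wave, which reproduces. That is 3000 per arm.

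**Inputs from Study context (2013 state survey).**
- LGB share: 3.0% + 7.5% = 10.5%, or 3000 × 0.105 = 315 LGB students per arm per wave.
- Seriously considered suicide: 38.3% of LGB students, 15.6% of all students.
- Implied non-LGB rate: (0.156 − 0.105 × 0.383) / 0.895 = 0.129. This is back-calculated; the article does not state it.

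**Assumptions, not in the documents.** The intervention-arm LGB share rises to 13% and the control arm stays at 10.5%. No student's risk changes. Newcomers to the LGB group have risk m, varied from the non-LGB to the LGB rate.

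**Formulas.**
- LGB rate after the shift = (0.105 × 0.383 + 0.025 × m) / 0.13
- Non-LGB rate after the shift = (0.156 − 0.13 × new LGB rate) / 0.87
- Spurious interaction odds ratio = (LGB odds ratio, after vs before) / (non-LGB odds ratio, after vs before), because the control arm does not move.

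Example, m = 0.25: LGB rate = (0.0402 + 0.00625) / 0.13 = 0.357, odds ratio (0.357/0.643) / (0.383/0.617) = 0.90. Non-LGB rate = (0.156 − 0.0465) / 0.87 = 0.126, odds ratio 0.97. Interaction = 0.90 / 0.97 = 0.92 (before rounding, 0.896 / 0.969).

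| Newcomers' risk m | LGB rate | LGB OR | Non-LGB rate | Non-LGB OR | Interaction OR |
|---|---|---|---|---|---|
| 12.9% (non-LGB rate) | 33.4% | 0.81 | 12.9% | 1.00 | 0.81 |
| 25% | 35.7% | 0.90 | 12.6% | 0.97 | 0.92 |
| 32% | 37.1% | 0.95 | 12.4% | 0.95 | 1.00 |
| 38.3% (LGB rate) | 38.3% | 1.00 | 12.2% | 0.94 | 1.07 |

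The overall rate stays at 15.6% in every row. The non-LGB odds ratio is what a condition × change term would pick up if the LGB dummy were coded 0/1: it can reach 0.94 with no student helped.

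**Other assumed shares.** With a 12% share the interaction odds ratio runs from 0.87 to 1.04; with 15%, from 0.71 to 1.13. Suicide attempts (28.5% LGB, 9.4% overall) at a 13% share: 0.81 to 1.10. If the share moves equally in both arms, the spurious interaction is exactly 1.00.

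**Against sampling error.** For 2015 versus one follow-up wave, ignoring clustering and weights, the standard error of the log interaction odds ratio at a 13% share and m = 12.9% is √(0.0518 + 0.0133) = 0.26, the two parts being the LGB and non-LGB cells. Log 0.81 is about −0.21, or 0.8 standard errors. A two-sided 5% test would then reject about 13% of the time. With newcomers' risk halfway between the groups (interaction OR 0.93), it would reject about 6% of the time.

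**The case against.** A reader might infer that RLAS is designed to raise LGB identification and will therefore produce a false benefit. The documents do not support that. No strategy in Table 1 has that aim, and the Background ties disclosure to victimisation, not to how survey items are answered. Nor is a shift confined to the intervention arm given: Aim 3 allows for diffusion to control schools and notes that many schools may already use some strategies. A shift common to both arms, such as a general rise in identification, does not in itself bias the contrast.

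Other points for the plan also stand:

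- The 0.81 needs newcomers at exactly the non-LGB risk, the extreme end of the range. At full LGB risk the same shift works against the hypothesis.
- The bias is modest beside sampling error for shifts of 1.5 to 2.5 points.
- The rates are 2013 state figures, not the 2015 baseline of the 40 schools.
- Hypotheses 1–5 compare intervention with control schools in the whole population; the LGB contrast is an added question.
- With unlinked cross-sections, identity before the intervention is not available, so current identity is the workable measure.

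Reclassifying students by the same-sex-contact item might look like a way out. It is not: the 2013 survey was the "first to include questions about same-sex sexual contact and sexual identity", but Aim 2 does not list the contact item for the trial waves, and it would also be a self-report after randomisation.

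Finally, sensitivity analyses are commonly left to a statistical analysis plan. That is fair for their detail. It does not answer the main point, because the article itself fixes the model and the reading of its three-way term.

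**Conclusion.** The concern holds in a limited form. The documents establish that LGB status at follow-up is a post-randomisation variable and that the model conditions on it. They do not establish that the intervention changes it. If it does so differently by arm, the LGB interaction is biased, in a direction that depends on the unknown risk of newcomers: at an assumed 13% share it crosses from apparent benefit to masked benefit at a newcomers' risk of about 32%.

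Two stronger conclusions do not follow. A spurious LGB benefit is one possibility and not the expected result. The randomised comparison of all students is not compromised, because relabelling leaves the overall rate unchanged. That protection belongs to a comparison that does not condition on LGB status, and the article's only stated model does condition on it. The size rests on the 2013 state rates and on assumed shifts for which the documents give no figure. The change is worth making because it is cheap and protects both the main result and the reading of the LGB result.

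**What to change.** 1. Estimate the confirmatory condition × change effect for hypotheses 1–5 from a model without LGB terms. Use the LGB model only for the effect-modification question.
2. Analyse LGB share as an outcome by condition and wave, in the same weighted three-level logistic model.
3. Describe the LGB × condition × change result as conditional on a variable measured after randomisation. If LGB shares diverge by arm, report a sensitivity analysis in which newcomers' risk ranges from the non-LGB to the LGB rate, and show where the conclusion changes. The LGB result need not hold in every scenario to be reported.

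Cost: a few extra analyses of data already planned for collection, and a more cautious LGB claim. If shares do not diverge, that claim is on firmer ground.
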